### Outcome measurements

Measurements will be taken at baseline, immediately post-intervention (i.e., within 7 days of completion of the intervention) and at 6-month and 12-month follow-up points. All follow-up assessments will be conducted by a researcher blinded to the participant's group allocation. The researcher conducting the data entry process will be blinded to group allocation.

#### Baseline data

Socio-demographic data will be collected at baseline including the participant's age, gender, martial status, educational attainment, current work status, employment history (i.e. industry currently/previously employed in), insurance type, the nature of the musculoskeletal injury/condition and the time since their injury.

#### Primary outcome measure

Readiness for return to work: This will be evaluated using the Readiness for Return-to-Work (RRTW) scale [17], a 22-item scale which applies the readiness for change model to identify individual and social factors impacting on an individual's ability to initiate and maintain behaviour change i.e. return to work after an injury. The psychometric properties of the scale have been evaluated and found to be acceptable [17]. Six dimensions have been identified of which four are relevant for those not working and two for those working. The non-working dimensions are: Pre-contemplation; Contemplation; Prepared for action - behavioral; and, Prepared for action - self evaluative. The two dimensions for those working are Uncertain maintenance and Proactive maintenance. The mean value for each dimension is calculated with a higher score in a particular stage indicative of the level the individual is at. For the purposes of this study, readiness for return to work will be determined by higher scores in the Prepared for action - self evaluative, Uncertain maintenance, and Proactive maintenance dimensions. The latter two stages were included to ensure that those working were not excluded on the basis of having returned to work. Those in the Prepared for action - self evaluative stage will be classified as ready to return to work to avoid misclassifying those who are found to be ready for return to work but have been unable to obtain employment.

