## Discussion

Significant decisions made by this project team in developing this methodology are now outlined:

• Whether a generic self-management program would meet the needs of this population was an issue. It was decided it would, with the addition of two new modules described above.

• The project industry partners advised that co-morbidity, especially with psychiatric conditions, was common and an issue of concern to them. It was decided to include people with psychiatric co-morbidity, but to exclude those for whom the primary cause of their claims was a psychiatric condition or a significant non-musculoskeletal condition.

• There were some different views about the best duration of condition to include in the study. Researchers initially favoured acute or sub-acute conditions based on the knowledge that earlier interventions are usually more likely to be acceptable. Industry partners favoured chronic conditions as knowledge about how to deal with these is most lacking. A final compromise was cases of more than 3 months duration (i.e. just chronic) but not more than 3 years.

• Defining what was meant by compensation was not as simple as expected. Researchers were keen to include people on a broad range of compensation schemes, specifically workers compensation, transport accident compensation and disability benefits. The industry partners who were contributing some funds became concerned as it appeared that the study population may be predominantly people on disability benefits given the original recruitment strategy. In response the recruitment strategy was broadened to that described above to redress the imbalance.

• Consideration was given to whether to include return to work status as the primary outcome measure. However, to avoid the ambiguity surrounding the definition of return to work and to ensure we capture a complete picture of the complex return to work process, we decided to employ readiness for return to work as our primary outcome measure [21].

• Defining a scope for the economic evaluation which was feasible within the scope of this project yet valuable was a challenge. Ultimately it was agreed to conduct a cost-effectiveness and partial cost-benefit study as described.

Close collaboration between the researchers and industry partners during the formative stages of the development of the methodology proved to be important in ensuring the research would meet the needs of industry.

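### As the rule reads, being at work decides the primary outcome, so participants already working at enrolment start as successes in both arms, and baseline adjustment of this outcome is not clearly stated

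*Protocol article*

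**What the plan says.** All references are to the protocol article.

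- **Primary outcome measure.** On the Readiness for Return-to-Work scale, "Six dimensions have been identified of which four are relevant for those not working and two for those working". The working pair is named: "The two dimensions for those working are Uncertain maintenance and Proactive maintenance". On staging: "The mean value for each dimension is calculated with a higher score in a particular stage indicative of the level the individual is at". Readiness is "determined by higher scores in the Prepared for action - self evaluative, Uncertain maintenance, and Proactive maintenance dimensions". No numerical cut-off is given. The reason for counting the two working stages is stated: "The latter two stages were included to ensure that those working were not excluded on the basis of having returned to work".
- **Participants.** Volunteers must have been working when the injury or disorder began. Nothing requires them to be off work at enrolment.
- **Baseline data.** Current work status is recorded.
- **Randomisation.** Stratification is by state only.
- **Data Analysis.** The proportion ready is analysed by logistic regression, with 12 months as the time point of primary interest. Inclusion of baseline measures as covariates is stated for continuous outcomes.
- **Discussion.** Readiness was preferred to return-to-work status partly "to avoid the ambiguity surrounding the definition of return to work".

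**The concern.** A working participant has two dimensions, and whichever scores higher leads to the classification 'ready'. The endpoint therefore becomes: working, or not working and highest on Prepared for action - self evaluative. For people at work the scale adds nothing to the binary result. The definition of working, which the authors wished to keep out of the primary outcome, decides it.

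Two consequences follow. First, anyone working at enrolment is a success on day 0 in either arm and can only stay so or become a failure. If such people are numerous and mostly stay in work, they dilute the contrast between arms. Second, a positive result could be entirely a difference in employment, and a null result could reflect dilution. The single proportion ready cannot tell these apart.

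**Working it through.** **1. The classification.** Set the statements of the primary outcome section side by side: working people have two dimensions; the higher mean gives the stage; both of those stages count as ready. With no cut-off, no working person can be classified as not ready.

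**2. The plan's sample size.** Inputs from the Participants section: 30% vs 45% ready, 80% power, 10% loss, 183 per arm. Assumed: two-sided alpha 0.05, which is not stated. With p̄ = 0.375:

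n = [1.960 × √(2 × 0.375 × 0.625) + 0.842 × √(0.30 × 0.70 + 0.45 × 0.55)]² / 0.15² = 162.4, so 163 per arm.

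163 / 0.90 = 181.1, so 182, against 183 stated. The figure reproduces to within one participant. Evaluable per arm: 183 × 0.90 = 164.7.

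Power = Φ{[d − 1.960 × √(2p̄(1−p̄)/n)] / √[(p₁(1−p₁) + p₂(1−p₂))/n]} = 0.81 at n = 164.7.

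**3. Illustration of dilution.** Let w be the share working at enrolment and still working at 12 months in both arms. The article gives no value; w = 10% and 20% are assumptions.

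- *Model A:* control stays at 30% overall, and the 15-point gain occurs only among the rest. Intervention rate = 0.30 + 0.15(1 − w).
- *Model B:* the rest are ready at 30% vs 45%. Rates = w + 0.30(1 − w) and w + 0.45(1 − w).

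| w | Model A rates | Power | Model B rates | Power |
|---|---|---|---|---|
| 0% | 30.0% vs 45.0% | 0.81 | 30.0% vs 45.0% | 0.81 |
| 10% | 30.0% vs 43.5% | 0.72 | 37.0% vs 50.5% | 0.70 |
| 20% | 30.0% vs 42.0% | 0.62 | 44.0% vs 56.0% | 0.59 |

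Model A is not carried to w = 30%. There it requires (0.30 − 0.30)/0.70 = 0% ready among all other controls, which is a boundary case and not a planning scenario.

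**4. The other reading of 30% vs 45%.** If those figures already include baseline workers, power stays at 0.81 by construction. The rest must then move from (0.30 − w)/(1 − w) to (0.45 − w)/(1 − w): from 22.2% to 38.9% at w = 10% (16.7 points), or from 12.5% to 31.3% at w = 20% (18.8 points).

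**5. What adjustment recovers.** A simulation assuming that 90% of baseline workers stay in work in both arms gave power of about 0.73 without and 0.77 with baseline status in the logistic model at 10% working at baseline, and about 0.61 and 0.67 at 20%.

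**The case against.** The strongest reply is that the rule is intended. In a return-to-work trial, a person back at work is a success, and the article says why both working stages count. The Discussion also gives a second reason for choosing readiness, a fuller picture of the return-to-work process, which fits a composite of working and ready-but-unemployed. This stands. It supports keeping the classification and argues against recasting Uncertain maintenance as not ready. It does not address people who were working before the intervention began.

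Further points on that side, and what remains of each:

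- A reader might infer that everyone at work succeeds whatever they score. That is the natural reading, but it is an inference. A threshold in the full protocol could let a working person be not ready.
- A reader might infer that baseline workers carry no information. They can fail by leaving work, and the Background section counts retaining employment among the aims of vocational rehabilitation. An effect on job retention would show.
- A reader might infer that the trial is underpowered. The article does not support this: the sample size reproduces, the share working at baseline is unknown, and 30% vs 45% may already include them. The article describes the programme as tailored to people seeking to return to work, and reports concern that recruits might be mostly on disability benefits. Neither suggests a large share.
- Return-to-work status is a secondary outcome, so a difference in employment would be visible. It would still not show how much of the readiness result comes from each component.
- The article introduces logistic regression as a similar approach straight after stating baseline covariates for continuous outcomes. This may be meant to carry the adjustment over, but it does not say so.
- Covariates and extra tables are often left to an analysis plan. True, but the rule that makes baseline status matter is fixed here, and baseline adjustment is stated for one outcome type only.

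**Conclusion.** The point holds in a limited form. On the most natural reading, the primary outcome reduces to work status for anyone at work. People working at enrolment are eligible, start as successes in both arms, and are not clearly adjusted for in the binary primary analysis. Randomisation prevents bias, so what is at stake is power and interpretation.

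The size is not known. A fall from 0.81 to roughly 0.70 at 10% working throughout, or 0.60 at 20%, is an illustration. It rests on an assumed share, on full retention in both arms, and on the 15-point gain being confined to the rest. If the planning proportions already allow for baseline workers, nominal power is unchanged and the cost is the larger gain needed among the others. The conclusion on classification rests on there being no unstated cut-off.

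**What to change.** Keep the classification and the sample size. Before the first follow-up data are analysed, specify:

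1. **Baseline status in the 12-month primary logistic model**, as one factor with three levels: working; not working and ready; not working and not ready. Use one factor because working implies ready, so separate terms for work and readiness would overlap. State a penalised fit if a level has no failures, which could happen among baseline workers.
2. **The 12-month outcome by arm and component:** working, with Uncertain and Proactive maintenance shown separately; and not working but in Prepared for action - self evaluative.
3. **A supportive analysis** of participants not ready at baseline.

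If the full protocol contains a score cut-off, state it with the primary outcome.

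*Cost:* a few lines of analysis wording and a few extra tables, all from data already planned for collection. The supportive analysis has fewer participants and a wider interval. The adjusted odds ratio is conditional on baseline status and should be labelled so.

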#### Secondary outcome measures

Secondary outcomes include return to work status, health efficacy, and general health status.

• Return to work status will be documented.

• The Health Education Impact Questionnaire (heiQ™) is a reliable measure with high construct validity, designed to evaluate outcomes from patient education and self-management interventions for people with chronic conditions. It comprises eight domains to assess more proximal program outcomes [18].

• The SF-12v2^® ^Health Survey will be used to measure health status. It consists of 12 items from the widely-used SF-36 Health Survey and provides summary assessment measures of physical and mental health [19].

#### Economic outcome measures

The relative efficiency of adding the self-management intervention to usual vocational rehabilitation care will be assessed through cost and outcome data. Incremental cost-effectiveness ratios (ICERs) will be calculated in relation to the four outcome measures and will be estimates of the extra cost from adding the SMRTW intervention per extra unit of outcome/effect, e.g. the extra cost per extra participant classified as ready to return to work or per extra participant who returned to work. That is;(1)

where the subscripts '*I*' and '*C*' indicate the intervention and control groups, respectively. A partial cost-benefit (or cost) analysis will assess the net benefit, or cost, from adding the intervention. This measure is the difference (in dollars) in the benefits and costs between those who received the intervention and those who did not. Specifically;(3)

This analysis is referred to as a partial cost-benefit analysis (or cost analysis) as the benefit of the SMRTW program will be measured only in relation to participants' production of paid and unpaid work. Other potential benefits of the program such as gains in health status or health efficacy will not be estimated or included, and willingness-to-pay for the intervention will not be determined.

### Procedures

#### Preparation of Facilitators

The SMRTW program will be facilitated by two people: a lay facilitator trained in the self-management model and a vocational rehabilitation practitioner. The practitioners (n = 5) are employees of one of the project's industry partners, a national provider of vocational rehabilitation services. They will undertake an accredited four day train-the-trainer training program in self-management conducted by Arthritis Queensland.

A flow chart of the trial is presented in Figure 1. The recruitment period will be 18 months. Participants will be notified by the project manager via telephone when sufficient participants are recruited to constitute an intervention, and control group. This notification will occur up to two weeks prior to the commencement of an eight-week intervention period. The self-management sessions will be conducted at the offices of the vocational rehabilitation provider involved in the research. Outcome data will be collected via a telephone interview. In addition, to assess the uptake of the intervention, recruiting organisations will be asked to record the number of non-volunteers and their reasons for not participating.

**Figure 1 F1:**
[figure not shown]
**Flow chart of the research protocol**.

### Data Analysis

Analysis of the effectiveness of the SMRTW program will be performed on an intention to treat basis and per protocol. Primary outcomes of interest are those collected at 12 months post-intervention. The differences in the mean scores of the continuous variables will be analyzed using multivariate regression and the difference in the proportion of the dichotomous outcomes (e.g. the proportion 'ready to return to work') will be analyzed using logistic regression.

Continuous outcome measures will be analyzed using multi-level modeling to describe within participant differences over time and to account for the repeated measures design component of the study. In the modeling of continuous outcomes, the baseline measures collected pre-intervention will be included as covariates in the model. Based on the results observed, participant, time and intervention will be defined as fixed or random effects as appropriate. Similarly, multivariate logistic regression will be used to assess dichotomous (1/0) outcomes. The effect of the SMRTW program on the outcomes at the earlier time points (i.e. immediately and 6 months post-intervention) will also be analyzed after appropriate adjustments to the significance level to account for multiple testing.

In regards to the economic evaluations, service utilisation, cost and work outcome data will be obtained from the questionnaires administered to participants at the four data collection time points. Estimates of these measures for the intervening time periods shall be determined by linear interpolation. Summary data on the measures will be presented and compared statistically for the two groups.

To derive the ICERs, the cost-effectiveness analyses will be performed from the perspective of payers e.g. insurers and/or government. Estimated costs to these funders will include their expenditures on income/disability benefits, and vocational rehabilitation and health care services. Utilisation data for vocational rehabilitation and formal (e.g. general practitioner attendances and medication use) and informal health or social care services (e.g. community services) will be used to estimate the costs. In contrast, the partial cost-benefit (or cost) analysis will adopt a societal perspective in relation to costs. Thus, costs to participants and their families (e.g. time and travel costs) shall be estimated and added to the estimates of costs to payers. Sensitivity analyses may be conducted to allow for uncertainty in key assumptions or variables.

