### Participants

Participants will comprise eligible volunteers who are clients either referred to a national provider of occupational health services and vocational rehabilitation or referred directly to the trial by their insurer. Recruitment will be undertaken in two Australian cities. To be eligible for the study volunteers will have: a diagnosed, compensated musculoskeletal disorder of 3 months or more but not longer than 3 years in duration; been working at the time of the injury/onset of the chronic disorder; and English language and literacy skills that are adequate to complete the study requirements including participating in the self-management course. In addition, there must be written agreement by the payer (insurer) for the individual to participate. Individuals will not be eligible if they have signs and symptoms suggestive of non musculoskeletal conditions (e.g. tumour, systemic illness, inflammatory disease or infection), their primary condition is a psychological/psychiatric or neurological disorder, or if they have previously participated in a vocational rehabilitation, chronic pain, functional restoration or work hardening program as these may contain a self-management component.

The sample size calculation was based on the primary outcome readiness for return to work status at 12 months post-intervention. A power calculation was performed assuming that the proportion ready to return to work in the usual care group would be 30% and the proportion in the self-management group would be 45%. Accounting for a 10% loss to follow-up, a total of 183 participants were required in each study arm (total n = 366) for the study to achieve 80% power.

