### Intervention

The control group will receive usual vocational rehabilitation only. The intervention group will receive vocational rehabilitation plus the self-management intervention which has been termed Self-Management for Return to Work (SMRTW). It comprises eight, two-hour weekly sessions specifically, the six modules of the CDSMP plus two new modules relevant to a vocational rehabilitation setting. The SMRTW program will be conducted for groups of 8-10 participants. The new modules were developed to compliment the format and approach of the CDSMP. In order to be classified as having received the intervention, participants must attend at least five of the eight sessions including at least one of the new module sessions.

In developing the two additional modules, the research team consulted industry partners including a national leader in occupational and vocational rehabilitation and experts in self-management training. The (new) module titled *Navigating the System *aims to: assist the client understand the agency funding their rehabilitation, its function and services; encourage them to use problem-solving skills to deal with 'system' issues; and, enhance their knowledge of the various persons in the 'system' and their respective roles. The (new) module titled *Managing Return-to-Work *aims to assist the client to understand: their role in the return to work process; the factors enhancing and limiting the success of return to work; and, the implications of having people with injuries in the workplace for employers and co-workers. As this is the final module delivered in the program, participants are also encouraged to reflect on the skills they have learnt during the program and to plan for their futures.

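### The cost-benefit contrast is worded by receipt of the program instead of by randomised arm, and the plan does not say whether intention to treat or per protocol decides the effectiveness hypothesis

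*Protocol article*

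**What the plan says.** Three places in the protocol article bear on this.

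- **Data Analysis:** "Analysis of the effectiveness of the SMRTW program will be performed on an intention to treat basis and per protocol". No order of precedence is given. Later in the section, the economic measures are to be compared between the two groups.
- **Intervention:** to count as having received the program, "participants must attend at least five of the eight sessions including at least one of the new module sessions". The control group receives usual vocational rehabilitation only and has no sessions to attend. The article gives no other adherence rule and does not define the per-protocol set.
- **Economic outcome measures:** the subscripts in the incremental cost-effectiveness ratio stand for the intervention and control groups. The partial cost-benefit measure, defined next, is the dollar difference in "the benefits and costs between those who received the intervention and those who did not".

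**The concern.** Receipt of the program is a defined term in this article, and it is decided by attendance after randomisation. Taken at its word, the cost-benefit definition moves people who were randomised to the program but attended too few sessions out of the intervention side, along with the cost of the places they were given. The two economic analyses would then rest on different comparisons, and only the cost-effectiveness one would be randomised.

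A per-protocol analysis built on the same rule would drop low attenders from one arm and keep every control. The primary outcome is a readiness-to-change scale, so a link between attendance and outcome is plausible. It could run either way. Motivated people may attend more and also be readier. Equally, people who go back to work early may be unable to attend weekly sessions, yet would count as ready.

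If the two effectiveness analyses disagree, the article gives no rule for which one answers the first hypothesis. A per-protocol result could then be offered as evidence of effectiveness beside a null intention-to-treat result.

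**Working it through.** **The plan's own figure.** Under Participants, the article assumes 30% ready under usual care and 45% with self-management, and sets power at 80%. On size it says: "Accounting for a 10% loss to follow-up, a total of 183 participants were required in each study arm (total n = 366"). The significance level is not stated; I assume 0.05 two-sided. With pooled variance (mean proportion 0.375):

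n = [1.96 × √(2 × 0.375 × 0.625) + 0.842 × √(0.30 × 0.70 + 0.45 × 0.55)]² / 0.15² = 162.3, so 163 per arm.

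163 / 0.9 = 181.1, so 182 per arm against 183 stated. The figure reproduces. Evaluable per arm: 183 × 0.9 = 164.7, about 165.

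**Set-up for the bias.** Assume no true effect and 30% ready in both randomised arms. Let c be the share of the intervention arm that meets the attendance rule, and let a and b be the readiness rates in attenders and low attenders. Two conditions fix a and b:

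- c·a + (1 − c)·b = 0.30
- [a/(1 − a)] / [b/(1 − b)] = OR, the attender odds ratio

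The article gives neither c nor OR, so both are assumptions and are varied.

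**Per protocol** (low attenders dropped, all controls kept): difference = a − 0.30, with 165c against 165 participants. The rejection probability comes from the normal approximation to the two-proportion test.

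| c | OR | a | b | Difference (points) | Two-sided rejection |
|---|---|---|---|---|---|
| 70% | 0.5 | 25.5% | 40.6% | −4.5 | 13.0% (0.2% in favour of the program) |
| 70% | 1 | 30.0% | 30.0% | 0 | 5.0% |
| 70% | 2 | 34.1% | 20.5% | +4.1 | 11.2% |
| 80% | 1.5 | 31.6% | 23.6% | +1.6 | 6.1% |
| 90% | 2 | 31.3% | 18.5% | +1.3 | 5.7% |
| 60% | 3 | 38.5% | 17.3% | +8.5 | 29.7% |

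Worked line for c = 70%, OR = 2: 0.7 × 0.3406 + 0.3 × 0.2053 = 0.300. The group sizes are 115.5 and 165. The standard error is 0.0564 under the null and 0.0567 at these rates. Upper tail: (1.96 × 0.0564 − 0.0406) / 0.0567 ≈ 1.23, a probability of about 0.109. The lower tail adds about 0.004, giving about 11%.

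The intention-to-treat contrast stays at zero bias and 5% error in every row.

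**As treated** (the cost-benefit wording read literally, shown on readiness): low attenders join the controls. For c = 70%, OR = 2, the comparison rate is (165 × 0.30 + 49.5 × 0.2053) / 214.5 = 27.81%. The contrast is 34.06% against 27.81%, about +6.2 points. For OR = 0.5 it is 25.46% against (165 × 0.30 + 49.5 × 0.4059) / 214.5 = 32.44%, about −7.0 points. The same mechanism would act on dollars, but the article gives nothing from which to compute that size.

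**The case against.** Four objections deserve weight.

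1. **A reader might infer that per protocol has equal standing with intention to treat.** The article does not say so. It names intention to treat first and gives per protocol no confirmatory role. A condensed article commonly leaves the ranking of analysis sets to a full protocol or analysis plan, and neither is shown. This stands: the missing ranking is a point to settle, not proof of a co-primary per-protocol analysis. The intention-to-treat analysis is planned and sound.

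2. **The attendance rule is not expressly tied to the per-protocol set.** It defines who received the program. An unseen definition could also exclude controls, for instance for exposure to self-management, which the planned case-file audit is meant to gauge in usual care. This stands too. Still, it is the only adherence rule in the article, and that rule cannot act on controls.

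3. **A reader might infer that an as-treated cost-benefit analysis is planned.** The phrase may be loose shorthand for the two arms, as the neighbouring cost-effectiveness definition and the Data Analysis wording suggest. The equation that might settle it is not readable in the text available. So the intention is uncertain. The conflict in wording is not, because the phrase reuses a term the article has defined by attendance.

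4. **A reader might infer that the bias must favour the program.** It need not. If early return to work keeps people from sessions, the odds ratio falls below 1 and the program is penalised. If attendance is not prognostic, there is no bias.

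**Conclusion.** The point holds in a limited form. The cost-benefit sentence, read with the article's own definition of receipt, is a non-randomised contrast that contradicts the group-based wording used for the other economic analysis. Separately, the article does not say which analysis set decides the first hypothesis, and its only adherence rule can remove people from one arm alone.

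The consequence is conditional on attendance being related to outcome. At 70% attendance the per-protocol difference under a true null runs from about −4.5 to +4.1 points as the odds ratio goes from 0.5 to 2. With high attendance the distortion is small. At the heaviest setting shown (60%, odds ratio 3) the spurious 8.5 points would be more than half of the 15-point effect the trial is sized for (8.5 / 15 = 57%). All of this rests on assumed attendance and prognosis, the article's 30% control rate and 10% loss to follow-up, and a two-sided 5% level that the article does not state. The documents do not support a claim that the trial's main effectiveness analysis is biased, or that the plan is bound to produce a false positive.

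**What to change.** - Under Economic outcome measures, define the cost-benefit difference as that between participants randomised to the intervention and participants randomised to control, to match the cost-effectiveness ratio.
- Under Data Analysis, state that intention to treat, by randomised arm, decides the readiness hypothesis and is the basis of both economic analyses.
- Label any attendance-based analysis supportive only, and say whether its set is defined by the attendance rule in the Intervention section.
- Optionally, add a complier-average estimate with randomised arm as the instrument, also supportive. It has a wider interval than per protocol. It also assumes that attending fewer than five sessions has no effect, which is doubtful for a skills course; any partial benefit would inflate the estimate. Labelling per protocol as supportive is enough without it.

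The cost is a few sentences of wording, plus one extra model if the optional estimate is wanted. The sample size and data collection do not change.

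### As written, the societal cost-benefit analysis counts income and disability payments as a cost while already valuing return to work as production, which exaggerates net benefit toward the arm with more paid work

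*Protocol article*

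**What the plan says.** The economic evaluation has two parts with different perspectives. The incremental cost-effectiveness ratios (ICERs) take the payer's view, and the Data Analysis section defines the payer's costs: "Estimated costs to these funders will include their expenditures on income/disability benefits, and vocational rehabilitation and health care services".

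For the second part, the same section says that "the partial cost-benefit (or cost) analysis will adopt a societal perspective in relation to costs", and it states how that cost is formed: "costs to participants and their families (e.g. time and travel costs) shall be estimated and added to the estimates of costs to payers". The payer total is carried over with no item taken out.

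The other side of the balance is in the Economic outcome measures section, where "the benefit of the SMRTW program will be measured only in relation to participants' production of paid and unpaid work". Net benefit is defined there in words: "This measure is the difference (in dollars) in the benefits and costs between those who received the intervention and those who did not". An equation follows in the article but did not survive text extraction. That is no fault of the plan.

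**The concern.** An income or disability benefit uses up no resource. It moves money from the insurer or government to the participant. From the payer's side it is a true cost, so it belongs in the ICERs. From the societal side the payer's saving, when a benefit stops, equals the participant's loss of that income, and the two cancel.

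The stated sum enters the payer's side only. When a participant regains a paid week, the analysis credits the production of that week as a benefit and also credits the payment no longer made as a lower cost. The second credit has no counterpart in society's resources.

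The partial cost-benefit analysis is one of the two planned economic analyses. It bears on the second hypothesis in the Background, that adding self-management uses resources more efficiently. All participants have a compensated disorder, so benefit payments may well be a material item. The error also grows with the effect the programme is meant to have.

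**Working it through.** The article states no figure for this analysis, so there is none to reproduce. The sample size calculation concerns readiness for return to work and does not enter. The check is an accounting identity followed by an illustration with assumed inputs.

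**Inputs from the article**
- Payer cost includes income/disability benefits, vocational rehabilitation and health care (Data Analysis).
- Societal cost = payer cost + participant and family cost (Data Analysis).
- Benefit = production of paid and unpaid work (Economic outcome measures).
- Net benefit = between-arm difference in benefits and costs, in dollars (Economic outcome measures).

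**Assumed inputs, not in the article**
- W: weekly wage, also taken as the value of a week's output.
- r: share of the wage replaced by the benefit, 0.50 to 1.00.
- w: between-arm difference in paid weeks per participant (intervention minus control), all of which would otherwise have drawn a benefit.
- c: extra resource cost per participant in the intervention arm, set at 2 weekly wages.

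**Formulas**
- As written: the cost difference is cW − rwW, because benefit payments fall by rW for each paid week gained. Net benefit = wW − (cW − rwW) = [(1 + r)w − c]W.
- With the transfer removed, or matched by the participant's loss of benefit income: net benefit = (w − c)W.
- Difference = rwW.

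A paid week is therefore credited at (1 + r)W instead of W. Unpaid work, and paid weeks that would have drawn no benefit, are not affected.

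**Results, in weekly wages per participant, with c = 2**

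| r | w = 2, as written | w = 2, transfer removed | w = 0, both | w = −2, as written | w = −2, transfer removed |
|---|---|---|---|---|---|
| 0.50 | +1.0 | 0 | −2 | −5.0 | −4 |
| 0.75 | +1.5 | 0 | −2 | −5.5 | −4 |
| 0.95 | +1.9 | 0 | −2 | −5.9 | −4 |
| 1.00 | +2.0 | 0 | −2 | −6.0 | −4 |

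At w = 2 a programme that just breaks even appears beneficial. At w = 0 there is no distortion. At w = −2 the loss is exaggerated by 1.0 to 2.0 weekly wages.

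The break-even point moves as well. With the transfer removed, the programme needs w = c = 2 weeks. As written it needs w = c/(1 + r), which is 2/1.5 = 1.33 weeks at r = 0.50 and 2/2 = 1.00 week at r = 1.00. Under these assumptions, a gain between that lower threshold and 2 weeks would be reported as a net benefit when it is a net cost.

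**The case against.** The strongest reply is that the text at hand does not settle the matter. The net-benefit equation, where the terms would be itemised, is not shown. The participant costs are introduced as examples (time and travel), so benefit income forgone could be among them, which would cancel the transfer. A societal perspective, properly applied, nets transfers out. The article is also condensed, and a fuller economic plan may say so.

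Part of this stands: an offset is possible, and the point has to be made about the plan as written. But the article does more than leave a detail open. It names benefits as a payer cost and then gives a rule for the sum that carries the payer total over whole. The two examples of participant cost give no hint of lost benefit income. The possible sensitivity analyses are meant for uncertain assumptions or variables and would not repair the structure of the sum. The label of a partial analysis is explained by the health and efficacy gains left out, not by any treatment of transfers.

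A reader might go further and infer that every week back at work is counted twice and that net benefit is overstated. The documents do not support that. The second credit is the full wage only if r = 1, and it applies only to paid weeks that would have drawn a benefit. The direction depends on which arm works more. Nor can r be read as a percentage error in net benefit: 100r% is the excess on the gross credit for those paid weeks, and its share of net benefit depends on costs the documents do not give.

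**Conclusion.** The concern holds for the plan as written. The stated summation rule does not fit the stated perspective, and no text shown excludes or offsets the transfer. The excess is rW per additional paid week that would otherwise have drawn a benefit. Net benefit is overstated if the intervention increases paid work, the loss is exaggerated if it reduces paid work, and nothing changes if the arms do not differ.

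No dollar figure can be given, because the article states no wage, replacement share, programme cost or expected gain in weeks. The excess of 1.0 to 2.0 weekly wages per participant rests on an assumed gain of two weeks and r from 0.50 to 1.00. It also takes output to be worth the wage and every gained week to displace a benefit.

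This should be fixed, but its reach is limited to one secondary economic analysis. The primary outcome, the sample size and the effectiveness analyses do not depend on it. Keeping benefits in the payer-perspective ICERs is correct.

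**What to change.** In the economic paragraphs of the Data Analysis section, state that the societal cost consists of payer costs without income and disability benefits, plus participant and family costs. The payer part then covers real resources only: vocational rehabilitation, health care and delivery of the programme. Alternatively, show benefits as a separate transfer line, with the payer's outlay matched by the participant's receipt, so that it sums to zero. Keep benefits as a cost only in the payer-perspective ICERs. The net-benefit equation should be checked against the same rule.

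If an offset was already intended, the same sentence makes it explicit. The change needs no new data, because benefits are already named as an item separate from the service costs. It can be made at any time before the economic analysis is run.
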